## 6. Trial hypotheses and objectives

The present study is designed to test the hypothesis that addition of MMF to comprehensive supportive care would be superior to supportive care alone in reducing the risk of clinical important kidney outcomes in patients with IgA nephropathy and at high risk of progressing to ESRD.

## 7. Research methods

### 7.1 Study design

This study is a prospective, open-label, randomized controlled, blinded endpoint (PROBE) trial. This trial will include adult patients with IgA nephropathy who are at high risk of renal progression.

During a 12-week run-in period, all participants will be treated with comprehensive supportive care, including blockade of RAS using losartan to reduce blood pressure to a target below 130/80 mmHg. In participants whose urinary protein excretion rate remained above 0.75g per day despite blood pressure control, the dose of losartan will be increased to the tolerable maximum daily dose as described previously. Participants will be advised for lifestyle modification to quit smoking, restrict high-salt intake, and avoid nephrotoxic drugs. Anemic patients with a hemoglobin level lower than 110g/L were treated with erythropoietin. Statin was used when necessary. Dietary sodium intake

were monitored by urinary sodium excretion rate (or chloride excretion rate in patients treated with sodium bicarbonate) measured by 24-hour urine sample.

By the end of run-in period, participants who have persistent proteinuria, defined as urinary protein excretion rate above 0.75g and lower than 3.5g per day, eGFR over 30 ml/min/1.73m^2, and those who are willing to participate the study entered the 3-year trial phase and will be randomly assigned to MMF plus supportive care or to supportive care alone. Participants who are not tolerable to losartan (eGFR decline over 30% of baseline or developing hyperkalemia) during run-in phase will not undergo randomization.

Participants will be randomly assigned to the MMF plus supportive care group received oral administrated MMF at a daily dose of 1.5g for 12 months and then tapered to a maintained daily dose of 0.75g to 1.0g for at least 6 months. Both MMF plus supportive care and supportive care alone group stayed on supportive care as in run-in period. Participants will continue to be followed at regular intervals for a planned 3 years.

## **7.2 Study drug**

### **(1) Drug information**

- Drug: Mycophenolate mofetil (MMF)
- Formulation: Mycophenolate mofetil tablets 0.25g/tablet
- Manufacturer: Hangzhou Zhongmei Huadong Pharmaceutical Co., Ltd

### **(2) Drug accountability**

The trained delegated study staff will acknowledge receipt of all shipments of the study treatments by emailing the signed investigator product receipt form contained in the shipment to the study center. The study treatments must be kept in a locked area with restricted access. The study treatments must be stored and handled in accordance with the manufacturer's instructions. The investigator or pharmacist will also keep accurate records of the quantities of the study treatments dispensed, used, and returned by each participant using an accountability form.

### **(3) Participant compliance**

Study medications will be distributed by the investigator or appropriately qualified designee. Participants will be instructed to bring their unused study drug to every visit. Compliance will be assessed by tablet counts with regard to the total number of tablets taken over the entire treatment period. Investigators and their study personnel will be instructed to be sure that all participants take their prescribed number of tablets each month. If a participant forgets to take the tablets on a particular day she/he should be instructed to continue as planned on the next day. The participant should not try to catch up by increasing the dose on the next day.

## **7.3 Concomitant medication**

Participants in this study, whether in the MMF or control arm, will all receive supportive care for IgA nephropathy. The investigator should strive to control the blood pressure to a target of 130/80 mmHg. Throughout the trial, all participants should receive losartan adjusted to the maximal tolerated dose. All participants will have dietary recommendations for CKD, e.g. Low-salt intake (<5 g per day). Participants will be advised to quit smoking and limit alcohol intake during the study as part of standard supportive care. Anemic patients with a hemoglobin level lower than 110g/L were treated with erythropoietin. Statins will be recommended when necessary. Dietary sodium intake

were monitored by urinary sodium excretion rate (or chloride excretion rate in patients treated with sodium bicarbonate) measured by 24-hour urine sample.

#### 7.4 Sample size

The sample size is estimated before the study with the use of nQuery Advisor software. Our preliminary study of IgA nephropathy showed that the three-year rate of the primary endpoint (doubling of serum creatinine, end-stage renal disease, and death) among patients with IgA nephropathy taking RAS inhibitors was 36%. It is estimated that MMF treatment will reduce this rate to 16%. Thus, the enrollment of 76 per group will provide the study with a statistical power of 80% at a two-sided significance level of 0.05. Considering 10% of participants lost to follow-up over 3 years, the final sample size was 84 per group.

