|-----------------------------|---------------------------------------------------------------------------------------------------------------------------------------------------------------------------------------------------------------------------------------------------------------------------------------------------------------------------------------------------------------------------------------------------------------------------------------------------------------------------------------------------------------------------------------------------------------------------------------------------------------------------------------------------------------------------------------------------------------------|
|                             | 
and lower than 3.5g per day, and those who are willing to participate the study entered the 3-year trial phase and will be randomly assigned to MMF plus supportive care or to supportive care alone. Patients who are not tolerable to RAS blockade (eGFR decline over 30% of baseline or developing hyperkalemia) during run-in phase will not undergo randomization.
 
In the trial phase, patients assigned to the MMF group received oral administrated MMF at a daily dose of 1.5g for 12 months and then tapered to a maintained daily dose of 0.75g to 1.0g for at least 6 months. Both MMF plus supportive care and supportive care alone group stayed on supportive care as in run-in period.
 |
| Study size           | 
The sample size is estimated before the study with the use of nQuery Advisor software. Our preliminary study of IgA nephropathy showed that the three-year rate of the primary endpoint (doubling of serum creatinine, end-stage renal disease) among patients with IgA nephropathy taking RAS inhibitors was 36%. It is presumed that MMF treatment will reduce this rate to 16%. Thus, the enrollment of 76 per group will provide the study with a statistical power of 80% at a two-sided significance level of 0.05. Considering 10% of participants lost to follow-up over 3 years, the final sample size was 84 per group.
                                                                            |

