## 3.4. Primary Outcomes

There are two primary outcomes.

1. The time to the first event of the composite outcomes, including:
  - a doubling of serum creatinine, defined as serum creatinine doubled over the baseline and confirmed by another measurement at least four weeks apart; or
  - onset of end stage kidney disease, defined by the need for maintenance dialysis or renal transplantation or kidney failure (defined as  $\text{eGFR} < 15 \text{ ml/min/1.73m}^2$  and need for dialysis or renal transplant, but renal replacement therapy is not available or patients refuse to receive renal replacement therapy); or death due to kidney or cardiovascular cause.
2. The time to progression of CKD, defined by a sustained  $\geq 30\%$  decrease in eGFR and to a level of  $< 60 \text{ ml/min/1.73m}^2$  if the baseline eGFR was  $\geq 60 \text{ ml/min/1.73m}^2$ , or  $\geq 50\%$  decrease in eGFR if the baseline eGFR was  $< 60 \text{ ml/min/1.73m}^2$ . The CKD progression endpoints were also verified by another measurement at least four weeks apart.

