### **4.4. Multiplicity Adjustment**

For the primary analysis, a two-sided p value of <0.025 was regarded as statistically significant. For the secondary and safety analyses, no multi-test adjustment was employed, and a two-sided p value of <0.05 was regarded as statistically significant. The outcomes are clearly categorized by degree of importance (primary, secondary) and a limited number of subgroup analyses are pre-specified.

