## **6.3. Efficacy Analyses**

### **6.3.1. Main Analyses of the Primary Outcomes**

- The number of the composite outcome (primary outcome 1) and its components by each treatment group in ITT.
- The number of disease progression (primary outcome 2) by each treatment group in ITT.
- Kaplan-Meier curves of cumulative survival rates of the two primary outcomes by two treatment groups in ITT.
- To perform log-rank tests on the two primary outcomes between the two treatment groups in ITT. A p-value of 0.025 will be regarded as statistically significant.
- Estimate the hazard ratios (and 95% confidence intervals) of the treatment for the two primary outcomes, respectively, using the Cox proportional hazard models, with and without covariate adjustment. The adjusting covariates include age, sex, BMI, SBP, eGFR, logarithm of UPE rate and individual Oxford MEST-C scores at baseline.

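### The 80% power is stated at two-sided 0.05, but the SAP tests each primary outcome at 0.025, where power for primary outcome 1 is about 72% to 75%

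*Combined protocol and SAP*

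**What the plan says.** **Sample size.** Protocol 7.4 and the study-size entry of the abstract assume a three-year event rate of 36% on RAS inhibitors, taken from a preliminary study, and 16% with MMF. From these, "the enrollment of 76 per group will provide the study with a statistical power of 80% at a two-sided significance level of 0.05". Allowing for 10% loss over three years, the target becomes 84 per group.

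**Decision rule.** SAP 3.4 states: "There are two primary outcomes". They are the composite of creatinine doubling, ESRD and kidney or cardiovascular death, and CKD progression; protocol 7.7 lists the same two. SAP 4.4, on multiplicity, states: "For the primary analysis, a two-sided p value of <0.025 was regarded as statistically significant". SAP 6.3.1 names the test, "To perform log-rank tests on the two primary outcomes between the two treatment groups in ITT", and repeats the threshold: "A p-value of 0.025 will be regarded as statistically significant". SAP 5.1 defines the ITT set as everyone randomized.

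**No reconciliation.** The SAP has no sample-size section that recalculates power at 0.025, and SAP section 7 records no changes to the planned analysis.

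**Endpoint behind the 36%.** The abstract describes it as "the three-year rate of the primary endpoint (doubling of serum creatinine, end-stage renal disease) among patients", with no death component. Protocol 7.4 gives the same rate for "doubling of serum creatinine, end-stage renal disease, and death".

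**The concern.** A power figure has meaning only for the test and threshold that decide the result. Here the sample size was set for one endpoint at 0.05, while the plan splits the significance level across two endpoints and tests each at 0.025. A reader of the protocol will believe that the trial has a 20% chance of missing the assumed effect on the composite; at the operative threshold that chance is larger. The practical stake is how a non-significant result on the composite is read: it would be taken as somewhat stronger evidence against benefit than the design supports. Type I error is not affected.

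Two gaps sit alongside this. Primary outcome 2 has no assumed rate, effect or power. And the two descriptions of the endpoint behind the 36% differ, so the key planning input is not tied to one definition.

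**Working it through.** **Inputs.** Control rate p1 = 0.36, MMF rate p2 = 0.16, n = 76 evaluable per group, 10% loss, 84 per group enrolled (protocol 7.4); 1:1 allocation (protocol 7.5); two-sided 0.05 (protocol 7.4) or 0.025 (SAP 4.4 and 6.3.1).

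**Step 1: reproduce the protocol's figure.** Two proportions, pooled variance under the null, no continuity correction:

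power = Φ[(p1 − p2 − z·s0) / s1], with s0 = √(2·p̄(1 − p̄)/n), s1 = √((p1(1 − p1) + p2(1 − p2))/n) and p̄ = 0.26.

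- s0 = √(2 × 0.26 × 0.74 / 76) = 0.07116
- s1 = √((0.2304 + 0.1344)/76) = 0.06928
- At 0.05, z = 1.960: (0.20 − 1.960 × 0.07116)/0.06928 = 0.874, so power = 80.9%.
- Solving for 80% power gives 74.3, so 75 per group.

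This matches the stated 76 and 80% closely. The protocol's arithmetic is sound for the threshold that it names.

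**Step 2: change only the threshold.**

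- At 0.025, z = 2.241: (0.20 − 2.241 × 0.07116)/0.06928 = 0.585, so power = 72.1%.
- 80% power at 0.025 would need 90.1, so 91 per group.
- With 76 per group held fixed, 36% vs 14.5% gives 79.8%. So 80% power corresponds to a treated rate of about 14.5% rather than 16%.

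**Step 3: the planned test.** The analysis is a log-rank test, so the two-proportion figure is a proxy. Under constant, proportional hazards, HR = ln(0.84)/ln(0.64) = 0.391. With 76 per group followed for three years, expected events = 76 × (0.36 + 0.16) = 39.5.

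| Method, two-sided 0.025 | n per group | Power |
|---|---|---|
| Continuity-corrected two-proportion | 76 | 65.4% |
| Fisher exact | 76 | 66.2% |
| Freedman log-rank | 76 | 69.6% |
| Pooled two-proportion (protocol's formula) | 76 | 72.1% |
| Log-rank, simulated, no loss | 76 | about 73% |
| Chi-square, exact power | 76 | 73.2% |
| Unpooled two-proportion | 76 | 74.1% |
| Schoenfeld log-rank | 76 | 76.2% |
| Log-rank, simulated, 10% exponential loss over 3 years | 84 | about 75% |
| Pooled two-proportion, no loss | 84 | 76.8% |
| Schoenfeld log-rank, no loss | 84 | 80.6% |

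The row closest to the planned analysis is the simulation with 84 per group and 10% loss: 75.2% over 20,000 runs, against 83.2% at 0.05. Only the Schoenfeld approximation with no loss at all reaches 80%, and no loss contradicts the protocol's own 10%.

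**Step 4: what cannot be computed.** The documents give no event rate or effect for primary outcome 2, and no information on the correlation between the two outcomes. Neither the power for outcome 2 nor the power to succeed on at least one outcome follows from the stated inputs.

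**The case against.** The strongest reply is that 72% describes a test and a sample that the plan does not use. It is a two-proportion power in 76 evaluable patients, whereas the plan is a log-rank test in everyone randomized, and patients lost to follow-up still contribute censored time. This stands. For the analysis as planned the figure is about 75%, a shortfall of about 5 points against 80% rather than 8, so both figures should be given and labelled.

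A reader might infer that the trial's decision rule has a 28% chance of missing the assumed effect. The documents do not support that. The 28% (100 − 72) covers primary outcome 1 alone, by the two-proportion formula. If success on either outcome counts, which is the usual purpose of splitting the significance level, the chance of at least one success cannot be lower than the power for outcome 1 and may be higher.

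A reader might also infer that protocol 7.4 counts death from any cause, and that the actual primary composite should be written in as the source of the 36%. Section 7.4 refers only to death, which may be shorthand for the cause-specific death in section 7.7. The 36% is an observed rate from a preliminary study that the documents do not show, and attaching it to another definition could make the text false.

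Finally, SAP 6.3.1 already requires hazard ratios with confidence intervals, which limits the risk of misreading a null result. That is fair and lowers the stakes. It does not make the power statement correct.

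**Conclusion.** Wrong as written. The protocol's power and the SAP's significance threshold contradict each other. At the operative two-sided 0.025, power for primary outcome 1 is about 72% by the formula that reproduces the protocol's figure (76 evaluable per group), and about 75% for the planned log-rank test (84 per group, 10% loss). Both take 36% and 16% as given; the log-rank figure also assumes constant, proportional hazards and exponential loss. With 76 per group, every method checked falls below 80%.

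This is an inconsistency between protocol and SAP rather than a slip in calculation. It changes no estimate or test. The difference in how the 36% endpoint is described is real but minor, and its numerical effect cannot be judged from the documents.

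**What to change.** Keep the 0.05 calculation on record as the basis of the original sample size. Add the following to protocol 7.4 and to the study-size entry of the abstract:

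> At the operative two-sided 0.025, power for primary outcome 1 is about 72% (76 evaluable per group, two-proportion formula) or about 75% (log-rank, 84 per group with 10% loss, constant and proportional hazards assumed). With 76 per group, 80% power corresponds to 36% vs about 14.5%. Primary outcome 2 was not separately powered, and the power to succeed on at least one primary outcome cannot be derived from the stated inputs.

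Separately, reconcile the abstract with section 7.4: state which endpoint definition produced the 36% in the preliminary study and how it differs, if at all, from the primary composite. Do not relabel the rate.

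The cost is wording only. No extra enrolment or change of analysis is requested; the downside for the sponsor is a less favourable stated power.

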#### 7.5 Randomization

All participants meeting inclusion and exclusion criteria and providing informed consent will be randomized to either the MMF plus supportive care group or supportive care alone group in a 1:1 ratio. A random sequence with a block size of 6 will be generated before the start of the trial and maintained by a party not involved in the conduct of the study. Randomization will be carried out via phone call.

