#### 7.6 Blind

This is an open-label, blinded end point trial. Both the participant and study personnel will be aware of the treatment assignment. An adjudicating committee, whose members will be unaware of patients' treatment assignments, review the data to determine which patient has reached study end points.

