## **Independent ethics committee (IEC) or institutional review board (IRB)**

In all countries where reference to an IEC/IRB is required, documented approval from appropriate IECs/IRBs will be obtained for all participating centers prior to study start. When necessary, an

extension, amendment or renewal of the IEC/IRB approval must be obtained and also forwarded to the study initiator and funder. The IEC/IRB must supply to the study initiator and funder, upon request, a list of the IEC/IRB members involved in the vote and a statement to confirm that the IEC/IRB is organized and operates according to applicable laws and regulations.

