## 3. Study Design

This study is a prospective, open-label, randomized controlled, blinded endpoint (PROBE) trial. This trial will include participants with IgA nephropathy who are at a high risk of disease progression.

Patients with IgA nephropathy were recruited at the renal division of Nanfang Hospital, Southern Medical University. After recruitment, the patients first entered into a 12-week run-in period, during which the patients were treated with comprehensive supportive care, including blockade of RAS using maximum tolerable daily dose of losartan to reduce blood pressure to a target below 130/80 mmHg and a urine protein excretion (UPE) below 0.75g per day. The participants were also advised for lifestyle modification, including quitting smoking, restricting high-salt intake, and avoiding nephrotoxic drugs. Anemic patients with a hemoglobin level lower than 110g/L were treated with erythropoietin. Statin was used when necessary. Dietary sodium intake were monitored by urinary sodium excretion rate (or chloride excretion rate in patients treated with sodium bicarbonate) measured by 24-hour urine sample.

The patients who were tolerable to losartan (<30% eGFR decline and without hyperkalemia) and proteinuria (0.75-3.5 g/day) at the end of run-in period were randomized to receive MMF plus supportive care or supportive care alone. The MMF plus supportive care group received a daily oral dose of 1.5g MMF for the first 12 months, followed by a maintenance daily dose of 0.75g to 1.0g for at least 6 months. Both MMF plus supportive care and supportive care alone group stayed on supportive care as in the run-in period. All participants were followed up at regular intervals for 3 years.

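### A fixed, disclosed block size of 6 in an open-label trial lets a well-placed staff member deduce about a quarter of allocations: an opening for selection bias that is cheap to narrow and to check.

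*Combined protocol and SAP*

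**What the plan says.** Protocol 7.5 sets 1:1 allocation and one block size: "A random sequence with a block size of 6 will be generated before the start of the trial". The list is "maintained by a party not involved in the conduct of the study", and "Randomization will be carried out via phone call".

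Treatment is open. Protocol 7.6 states: "Both the participant and study personnel will be aware of the treatment assignment". Only the endpoint committee and, under SAP 3.3, the statistical analysis group are kept unaware of assignments.

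The documents do not agree clearly on the number of recruiting sites. SAP section 3 says: "Patients with IgA nephropathy were recruited at the renal division of Nanfang Hospital". Protocol section 8 says: "documented approval from appropriate IECs/IRBs will be obtained for all participating centers prior to study start". Protocol 7.13 also speaks of sites in the plural, and no number is given anywhere.

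Neither document mentions stratification, varied block sizes or keeping the block size from site staff. Protocol 7.13 provides for investigators and site personnel to discuss the protocol, which prints the size.

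**The concern.** In a permuted block of 6 at 1:1, once three patients have gone to one arm, the rest of the block must go to the other. Anyone who knows the block size and has seen the assignments in order can work this out without sight of the list. If the coming arm is known, a decision about whom to randomize next, or when, can depend on it. The arms could then differ in prognosis at baseline. Blinded adjudication acts after enrolment and cannot correct that. The log-rank test of the primary outcomes (SAP 6.3.1) is unadjusted, so such a difference would enter it directly.

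**Working it through.** **Inputs.** Block size 6 and ratio 1:1 (protocol 7.5), hence 3 + 3 per block. Planned total 2 x 84 = 168 (protocol 7.4). Assignments visible to staff (protocol 7.6). One unstratified sequence, followed by one division (SAP section 3).

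**Plan's own figure.** The documents give no figure for predictability. The sample size serves here only to turn a percentage into a count. For 36% against 16%, two-sided 0.05 and 80% power, the pooled-variance formula gives 75 per group against the stated 76, and 76 x 1.10 = 83.6, rounded to the stated 84. That is close enough for this use.

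**Certain allocations, fixed size 6.** There are C(6,3) = 20 possible blocks. Of these, 12 end with one forced allocation, 6 with two and 2 with three:

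- Mean = (12 x 1 + 6 x 2 + 2 x 3)/20 = 30/20 = 1.5 per block.
- By position, the chance of being forced is 0 in positions 1 to 3, 10% in position 4, 40% in position 5 and 100% in position 6; 0.1 + 0.4 + 1.0 = 1.5.
- Closed form for a block of 2m: 2m/(m + 1). With m = 3, 6/4 = 1.5.
- Share = 1.5/6 = 25%. Over 168/6 = 28 blocks, 28 x 1.5 = 42 allocations.

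**Best guess, fixed size 6.** Always guess the arm with more places left, and toss a coin when they are equal. Expected correct guesses per block = m + 2^(2m-1)/C(2m,m) - 0.5 = 3 + 32/20 - 0.5 = 4.1. That is 4.1/6 = 68.3%, about 115 of 168, against 50% by chance.

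**Varied sizes.** The sets below are illustrative assumptions. The figures come from 1,500 simulated sequences of 168 allocations, with an observer who knows the set of sizes but not their order and uses the whole history. The first row is exact.

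| Block sizes | Certain | Of 168 | Best guess correct |
|---|---|---|---|
| Fixed 6 | 25.0% | 42 | 68.3% |
| 4, 6 | 5.4% | about 9 | 69.3% |
| 2, 4, 6 | 4.1% | about 7 | 70.1% |
| 4, 6, 8 | 2.2% | about 4 | 68.0% |
| 4, 8, 12 | 2.8% | about 5 | 65.9% |

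Varying the size removes most of the certainty. It barely changes the best-guess rate, and with small blocks raises it slightly.

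**Where discretion remains.** The randomization limits are laboratory values: 24-hour protein excretion above 0.75 and below 3.5 g, no eGFR fall over 30% or hyperkalemia on losartan, and eGFR not below 30 (protocol 7.8). Two routes are left. Protocol 7.1 makes entry to the trial phase depend on the patient's willingness at the end of run-in, which staff can influence. Protocol 7.10 asks only that visit dates be kept as closely as possible, which leaves some freedom in the timing and order of calls.

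**The case against.** The strongest reply is that concealment is adequate: an outside party holds the list and releases assignments by phone. This protects against reading or altering the list. It does not stop deduction from assignments already seen.

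Secondly, there is little to select on. Proteinuria and losartan tolerance are measured, Table 1 places consent at Visit 2, and randomization is fixed at Visit 5, 12 weeks later. This largely stands, and a reader who took those criteria to be matters of judgement would be wrong. The ability-to-comply criterion adds little, because it is applied before run-in, when the arm waiting at Visit 5 is hard to foresee.

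Thirdly, SAP 6.3.1 also plans Cox models adjusted for baseline eGFR, log protein excretion and other factors. This is a partial safeguard: it covers measured factors only and leaves the log-rank test unadjusted.

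Fourthly, the remedy may gain little or come too late. Best-guess success stays near 68%, so staff acting on guesses would be right about as often as before. The SAP speaks of recruitment and randomization in the past tense, so the list may be used up. Both points stand.

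A reader might infer that selection bias occurred, or that varied blocks would remove most of any bias. The documents support neither. They contain no enrolment data and give no basis for how far staff could shift prognosis, so no size of bias is claimed here.

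**Conclusion.** The point holds as a cheap improvement. For an observer who knows the block size and follows every assignment in order, a quarter of allocations are certain in advance: at least 1 and at most 3 per block, about 42 of 168 on average. Nothing in the plan prevents this.

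The figure assumes one unstratified list used by one division. That rests on the SAP alone; if several centres draw on the same list, none sees the whole sequence and the share is lower. The effect on the comparison depends on discretion that the laboratory limits narrow but do not close. What is shown is an opening for selection.

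**What to change.** 1. **Any unused part of the sequence:** have the party that holds the list regenerate it with randomly varying block sizes, for example 4, 6 and 8, known only to that party. Remove the block size from the protocol that site staff see. Certain allocations fall to about 2% (about 5% with 4 and 6 only).
2. **Whether or not enrolment is complete:** add to the SAP a comparison of baseline eGFR and urinary protein excretion between arms, separately for forced and unforced block positions. The planned tests in SAP 6.1 compare the arms only overall. The check uses baseline data already collected, plus allocation order and block boundaries from the list holder. It should be run after unblinding or by that party, since SAP 3.3 keeps the statistical group unaware of assignments.
3. **Reconcile** SAP section 3 with the plural-centre wording in protocol 7.13 and section 8, and state how many centres share the list.

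**Cost.** A new list, a change of protocol wording and one small analysis. The possible imbalance if recruitment stops within a block rises from 3 (half of 6) to 4 (half of 8).

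**Limit of the check.** With about 42 forced allocations, or 21 per arm, the standard error of an arm difference is sqrt(1/21 + 1/21) = 0.31 SD. It can reveal gross selection, but a null result would not exclude a modest one.
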